### Serious or unexpected adverse events

Any adverse events identified to be related to the study intervention, whether
serious or unexpected, as assessed by researchers or professionals involved in
the care will be immediately reported to the competent authorities, in
particular to the management of the unit, the management of the hospital and the
responsible REC. The patient will receive all necessary care to reverse or
minimize any damage resulting from the study. Given the suspicion of such
events, if the patient is in the intervention group, the intervention will be
interrupted, and the data will be analyzed according to an intention to treat
protocol, except in cases in which the patient or family members request
withdrawal of the individual from the study. We believe that safety should be
the priority in a randomized clinical trial. The absence of an external
committee in our study is the result of extensive discussion in the design of
the study, in which the safety of the intervention chosen and the additional
costs that the committee would represent to the project were considered. The
final decision not to include a monitoring committee was defined, described and
sent to the REC responsible for the original project.

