### Data collection

The following data will be collected from all patients: name, sex, age, race,
height, weight, hospital identification number, date of birth, etiological
diagnostic indicator of transplantation, pretransplantation Model for End-stage
Liver Disease (MELD) score, origin before transplantation (ICU, ward or home),
comorbidities (diabetes mellitus, heart failure, arterial hypertension,
nondialytic chronic renal failure, active cancer, previous stroke or transient
ischemic attack or immunosuppressive therapy in the last 30 days before
surgery), preoperative creatinine, donor risk index (DRI) and use of nephrotoxic
drugs in the week before transplantation.

The following intraoperative data will also be collected: anesthesia time, total
and cold ischemia time of the liver graft, presence of ischemia‒reperfusion
syndrome, time of admission to the ICU, use of blood products, antibiotic
prophylaxis, initial value of arterial lactate, peak arterial lactate, final
value of arterial lactate, use of basiliximab, use of fluids, type of fluids,
episodes of intraoperative hypotension and loss of fluids.

The following postoperative data will also be collected: length of hospital stay
after transplantation; length of stay in the ICU; time of mechanical
ventilation; duration of vasopressor use and maximum vasopressor dose; need for
renal replacement therapy; need for postoperative transfusion; primary graft
dysfunction; secondary graft dysfunction; need for retransplantation; surgical
site infection; Sequential Organ Failure Assessment (SOFA) score on admission to
the ICU; D1, D3 and D7; daily creatinine, to evaluate the presence of acute
kidney failure (AKI) in the first 28 days after transplantation or until
hospital outcome if this occurs before the described period; admission and
48-hour urinary NGAL; presence of surgical site infection in the first 7 days
after transplantation; arrhythmias requiring chemical or electrical treatment in
the first 7 days after transplantation; diagnosis of acute coronary syndrome in
the first 7 days after transplantation; volume of crystalloids infused in the
first 24 hours after surgery; volume of colloids infused in the first 24 hours
after surgery; diuresis in the first 24 hours after surgery; drainage output in
the first 24 hours after surgery; presence of major bleeding in the first 24
hours after surgery; need for transfusion in the first 24 hours after surgery;

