antibiotic prophylaxis in the first 24 hours after surgery; use of nephrotoxic
drugs in the first 7 days; immunosuppression in the first 7 days and maximum
tacrolimus level within 7 days; new surgery within 7 days after randomization;
ICU readmission for treatment of complications within 7 days after
randomization; need for retransplantation within 28 days and ICU and hospital
outcome in 28 days (discharge, hospitalization or death).

Data collection will be performed by an external professional (research nurse)
with no connection to the unit. This professional will have access to the data
described but will not have any role in the randomization and management of
patients participating in the study. Such data will be collected in an
electronic form via Redcap® and will remain protected by a
nontransferable password. The professional will perform serial evaluations to
ensure the follow-up of all patients until the 28th postoperative day. The final
result collected will be available, also by means of a password, to the external
professional in charge of the statistical calculations, as well as to the main
researcher.

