### Statistical analysis

The analyses will be performed according to the “intention-to-treat” principle;
all randomized patients will be included in the analysis according to the
treatment group to which they were randomly assigned. Summary statistics per
group, with treatment effects, 95% confidence intervals and p values, will be
presented for the primary and secondary outcomes. Continuous variables will be
tested for normality using the Shapiro‒Wilk test after graphic analysis by
histogram. Parametric continuous variables between two groups will be compared
with the unpaired *t* test and within the same group with the
paired *t* test. If analysis among more than two groups is
required, analysis of variance (ANOVA) will be used. Nonparametric continuous
variables will be evaluated using the Wilcoxon test or the Mann‒Whitney U test
between two groups and the Kruskal‒Wallis test between three or more groups.
Categorical variables will be evaluated using the chi-square test or Fisher’s
exact test, as appropriate. P values < 0.05 will be considered statistically
significant. The outcomes of hospitalization-free days or renal dysfunction over
time will be calculated based on the 7- and 28-day follow-up, respectively,
using Cox regression models. The calculations of survival curves will be
performed with the Kaplan‒Meier method. For the statistical analysis of
outcomes, the results will be adjusted for previous renal function, and logistic
regression will be used to adjust for other confounding factors that generate
inconsistency in the baseline that were not corrected by the randomization of
the study (use of nephrotoxic drugs, maximum tacrolimus level in the first week,
intraoperative fluid balance and intraoperative major bleeding). No statistical
adjustments will be provided for multiple comparisons in the case of secondary
outcomes, and therefore, we suggest that these be interpreted as exploratory
analyses.

The existence of missing data will be described in the publication and managed
with simple exclusion from the analysis. For this study, no interim analyses are
foreseen.

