□ **Acute renal dysfunction according to urinary NGAL assessment**

Number of days during the first 7 postoperative days that the patient was alive
and did not meet the following criteria for renal dysfunction: urinary NGAL
value > 150ng/mL. This outcome will be assessed at admission and at 48
hours.^(2)^

□ **Primary graft dysfunction - initial poor function subtype at 7
days**

Development of one of the following laboratory criteria within the first 7 days
after liver transplantation: bilirubin > 10mg/dL on the seventh day after
transplantation; international normalized ratio > 1.6 on the seventh day
after transplantation; alanine aminotransferase or aspartate aminotransferase
> 2,000IU/L in any of the first 7 days after transplantation.^(3)^

□ **Primary allograft dysfunction - primarily nonfunctional subtype at 10
days (Broering)**

Need for retransplantation in the first 10 days after transplantation or death
due to a nonfunctioning graft.^(3)^

□ **Major adverse kidney events in 28 days (MAKE28)**

The incidence of death, need for renal replacement therapy or persistent renal
dysfunction at 28 days after liver transplantation.^(4)^

□ **Days alive and hospitalization-free in 28 days**

Number of days among the first 28 postoperative days in which the patient was
alive and hospitalization-free.

□ **Major postoperative bleeding at 7 days**

Dichotomous outcome of bleeding that indicates, on the same day, the transfusion
of more than two units of packed red blood cells or the need for surgical
intervention indicated in the first 24 postoperative hours.

□ **Transfusion of blood components in 7 days**

Number of blood components transfused in 7 days separated into packed red blood
cells (one unit equal to one bag), fresh frozen plasma (one unit equal to one
bag), fibrinogen concentrate (one unit equal to 1g) and tranexamic acid (one
unit equal to 1g).

□ **Arrhythmias requiring chemical or electrical therapy within 7
days**

Description in the prescription or medical records of antiarrhythmic or
electrical cardioversion therapy for the first 7 days for treating abnormal
rhythm. A maximum of one event per patient will be considered dichotomously, as
the same event can be reentrant.

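### Excluding patients with missing data conflicts with the stated intention-to-treat analysis, and leaves MAKE28 undetermined for patients discharged alive before day 28 without renal replacement therapy

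*Protocol article*

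**What the plan says.** All references are to the protocol article.

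- **Analysis set (Statistical analysis).** The analysis is by intention to treat: "all randomized patients will be included in the analysis according to the" group assigned at randomization.
- **Missing data (Statistical analysis).** Missing data will be described in the publication and managed "with simple exclusion from the analysis". The rule is general and covers the primary and all secondary outcomes.
- **Withdrawal (Serious or unexpected adverse events).** After a suspected related event in the intervention group, the intervention stops and the data are analysed under an intention to treat "protocol, except in cases in which the patient or family members request" withdrawal from the study.
- **Creatinine window (Data collection).** Creatinine is recorded daily for 28 days or until "hospital outcome if this occurs before the described period". The same section lists the ICU and hospital "outcome in 28 days (discharge, hospitalization or death"), so discharge is a hospital outcome. It also has the research nurse "ensure the follow-up of all patients until the 28th postoperative day", but the data list contains no creatinine after discharge.
- **MAKE28 (Appendix 1).** "The incidence of death, need for renal replacement therapy or persistent renal" "dysfunction at 28 days after liver transplantation".

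**The concern.** A randomized patient whose outcome is missing cannot be both included and excluded. The withdrawal exception is a second departure from the stated analysis set. It sits in a sentence about the intervention arm of an open-label trial, so exclusions could differ between arms.

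For MAKE28 the problem is structural. Death and RRT make the composite positive whatever happens to creatinine afterwards. A patient who goes home before day 28 without RRT and survives has no day-28 creatinine, and the only rule the article gives for a missing value is exclusion. Being dropped therefore depends on recovering well enough to leave hospital, which the pressure target might itself influence. What remains is a sicker subset, possibly selected differently in each arm.

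**Working it through.** **1. Who has a determinable MAKE28 under the rules as written**

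| Status by day 28 | MAKE28 |
|---|---|
| Died, in or out of hospital | Event |
| Alive, had RRT | Event |
| Alive, no RRT, still in hospital | Determined by creatinine |
| Alive, no RRT, discharged before day 28 | No day-28 creatinine: excluded |

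Only the last row is lost.

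**2. What the exclusion could do to the MAKE28 rate.** The article gives no death, RRT or discharge rates, so every input here is an assumption. Let *e* be the proportion with death or RRT, *h* the proportion event-free and still in hospital at day 28, and *d* = 1 − *e* − *h* the proportion discharged without either. Assume persistent dysfunction in 40% of the *h* group and 15% of the *d* group.

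- All patients: *e* + 0.40*h* + 0.15*d*
- After exclusion: (*e* + 0.40*h*) / (*e* + *h*)
- Patients dropped: 174*d*

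| *e* | *h* | *d* | Dropped of 174 | All patients | After exclusion |
|---|---|---|---|---|---|
| 12% | 10% | 78% | 136 | 27.7% | 72.7% |
| 12% | 30% | 58% | 101 | 32.7% | 57.1% |
| 20% | 10% | 70% | 122 | 34.5% | 80.0% |
| 20% | 30% | 50% | 87 | 39.5% | 64.0% |

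A second grid used death 5–10%, RRT in a further 10–20%, 50–90% of the rest discharged early, and persistent dysfunction in 5–15% of the rest whether discharged or not. It drops 61 to 133 patients. Its mildest inflation is from 40.5% to 54.2% (death 10%, RRT 20%, half discharged early, dysfunction 15%). Its largest is from 28.7% to 78.1% (death 5%, RRT 20%, 90% discharged early, dysfunction 5%). The direction is the same in every cell; the size is not stable.

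**3. What it could do to the comparison.** Again by assumption, let *e* = 15% in both arms, with 60% of one arm and 70% of the other discharged early, so *h* = 25% and 15%.

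- All patients: 0.15 + 0.40×0.25 + 0.15×0.60 = 34.0%, against 0.15 + 0.40×0.15 + 0.15×0.70 = 31.5%.
- After exclusion: 0.25/0.40 = 62.5%, against 0.21/0.30 = 70.0%.

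The arm with the lower true rate shows the higher observed rate.

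**4. Primary outcome: reproduce the 174.** Sample size calculation gives 73.7%, an absolute reduction of 20 points (so 53.7%), 80% power and alpha 5%; two-sided testing is assumed. With unpooled variance:

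n per arm = [0.737×0.263 + 0.537×0.463] × (1.960 + 0.842)² / 0.20² = (0.1938 + 0.2486) × 7.849 / 0.04 = 86.8, so 87 per arm and 174 in total.

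The stated figure is reproduced exactly, which shows that it contains no allowance for exclusions.

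**5. Primary outcome: power if patients are excluded.** Exact binomial enumeration of the chi-square test at 73.7% versus 53.7%:

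| Analysed per arm | Excluded of 174 | Power |
|---|---|---|
| 87 | 0 | 79.1% |
| 83 | 8 (4.6%) | 76.8% |
| 78 | 18 (10.3%) | 75.2% |

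**6. Primary outcome: worst-case reach of missing data.** If a fraction *m* is missing in each arm and the observed difference is −20 points, the extremes for all randomized patients are −20(1 − *m*) ± 100*m* points. At *m* = 5% this is −24 to −14 points; at 10%, −28 to −8 points.

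**The case against.** The strongest reply is that the article never says a creatinine dated day 28 is required. Collecting creatinine to day 28 or hospital outcome fits a reading in which the last in-hospital value decides, and under that reading most of the MAKE28 loss disappears. The definition is also taken from a cited source, and detail of this kind may sit in the full protocol. This stands as a limit on the size of the problem. It does not remove it, because the article states exclusion as the rule and states no last-value convention.

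A reader might infer that most patients discharged alive are dropped from MAKE28. The documents do not support that. They give no discharge timing and no RRT share, and discharged patients who had RRT, or who die by day 28, still count as events.

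MAKE28 is one of 12 secondary outcomes, which the article says should be read as exploratory. That lowers the severity, though the label does not remove a bias.

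On the primary outcome, creatinine is measured daily over a short window and deaths within 7 days count as positive, so the main source of informative missingness is already closed. Nothing in the article suggests that 5% or 10% will be missing. A reader might also conclude that 174 is wrong; it is not, since it reproduces exactly.

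On withdrawal, the exception can be read as respecting withdrawn consent, which is a legitimate limit. That withdrawals would differ by arm is possible but not shown.

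**Conclusion.** The concern holds at moderate severity. Two parts rest on the text alone: the conflict between analysing everyone and excluding missing data, with the withdrawal exception as a second conflict; and the mismatch between a creatinine record that ends at discharge and a MAKE28 renal component placed at day 28. Taken literally, the stated rule keeps deaths and RRT cases and drops event-free patients discharged early.

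That missingness is informative. It can raise the observed MAKE28 rate and distort, or even reverse, the comparison between arms. How far depends on rates the documents do not give, so the tables above are illustrations and not estimates. For the primary outcome, the loss is about 2 to 4 points of power if 5% to 10% are excluded, with 174 carrying no allowance.

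**What to change.** 1. **MAKE28.** State that the renal component is assessed at hospital discharge or day 28, whichever comes first, using the last in-hospital creatinine.
2. **Primary outcome.** Replace simple exclusion. Classify a patient as positive if a 1.5-fold creatinine rise or death by day 7 was observed before data stop. Handle the remaining patients with incomplete data by multiple imputation from baseline creatinine, serial creatinine and arm, and report best-case and worst-case analyses. Do not count RRT by itself as a primary event: Main objective and Appendix 1 define the primary outcome by the creatinine rise, plus death within 7 days, and the 73.7% behind the sample size rests on the creatinine criterion.
3. **Withdrawal.** Reconcile the adverse-event section with Statistical analysis by keeping data collected before withdrawal where consent permits.

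These rules should be fixed before outcomes are examined by arm, because a rule chosen after seeing who is missing would not be credible. The cost is revised wording and modest programming on data already being collected. The main compromise is that the last in-hospital creatinine stands in for renal status at day 28, and the report should say so.

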### Subgroup analysis

As previously sent to the REC, the following subgroup analyses are planned:
present or absent previous renal dysfunction, present or absent liver graft
dysfunction, from home or hospitalized, use or nonuse of antibiotics for > 48
hours, serum tacrolimus value > 15 in 7 days, present or absent major
bleeding.

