### Secondary objective

To evaluate whether higher (85 - 90mmHg) *versus* usual MAP levels
(65 - 70mmHg) in the first 24 hours after liver transplantation surgery are
associated with 28-day mortality; retransplantation in 28 days; renal
replacement therapy in 7 days; surgical site infection within 7 days; days alive
and free of renal dysfunction in 7 days; renal dysfunction according to the
values of neutrophil gelatinase-associated lipocalin (NGAL) at admission and
after 48 hours; length of stay in the ICU; length of hospital stay; days alive
and hospitalization-free in 28 days; liver graft dysfunction (initial poor
function subtype) in 7 days; liver graft dysfunction (primary nonfunction) at 10
days and major adverse kidney events at 28 days (MAKE28).

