### Other outcomes (safety)

The safety outcomes to be assessed are the incidence of major postoperative
bleeding at 7 days, transfusion of blood components at 7 days and incidence of
arrhythmias requiring drug or electrical therapy at 7 days.

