### Randomization and blinding

Patients will be randomized within 2 hours of ICU admission after liver
transplantation using a simple 1:1 allocation sequence without group
stratification. The randomization will be performed electronically by the
randomization tool of the Redcap® system. The randomization sequence will
be generated *online* and entered into the system by a staff
member who will not participate in the participant tracking process, in
obtaining informed consent from the patient or in the clinical management of the
cases. The researcher will also not participate in the evaluation of the study
outcome data in order to ensure compliance with the allocation concealment
process.

As the interventions in both groups are based on target MAP levels to be followed
by the professionals involved in the care, the authors chose not to blind the
interventions, which, although possible, would be complex to perform in the
center in question. However, the professional responsible for collecting the
outcome data will be an external research nurse, with no affiliation with the
institution where the study is conducted and who is not involved with the care
offered to each patient. The same care will be taken to hire the statistician
who will analyze the results, ensuring that he or she will not be aware of the
allocated groups. To minimize the risk of bias, an objective primary outcome was
chosen based on test results measured by a certified laboratory.

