#### Specific management of the intervention group

The intervention will begin upon admission to the intensive care unit and
will continue for 24 hours after arrival at the ICU. The MAP target of the
intervention group will be 85 - 90mmHg in the first 24 hours after surgery.
The MAP will be measured using an invasive blood pressure catheter, measured
at 1-hour intervals during the first 12 hours and at 2-hour intervals
thereafter until the 24 hours have been completed (according to the protocol
of the ICU). Patients with a MAP lower than the established target may
receive fluids or vasopressors according to the discretion of the attending
physician to achieve the established target MAP.

Noradrenaline will be the initial vasopressor of choice, and the second will
be determined by the attending physician. In hypotensive patients with
reduced cardiac output as monitored by pulmonary artery catheter or
transthoracic echocardiogram, inotropes may be used at the discretion of the
assistant team. Patients who naturally present with a MAP > 90 mmHg even
after complete weaning from vasopressors will not receive additional
vasodilators to reduce the MAP to the study target. The use of vasodilators
in hypertensive patients for the purpose of blood pressure control will be
determined according to the decision of the attending physician.

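### At least two, and on the plain reading four, of the six planned subgroups are formed after randomisation, so treatment comparisons within them are not protected by it

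*Protocol article*

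**What the plan says.** Under Randomization and blinding: "Patients will be randomized within 2 hours of ICU admission after liver" transplantation. Under Specific management of the intervention group, the pressure target "will continue for 24 hours after arrival at the ICU".

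The Subgroup analysis section then lists six groupings. It begins "present or absent previous renal dysfunction, present or absent liver graft" dysfunction, goes on to origin (home or hospitalised) and antibiotic use beyond 48 hours, and ends "serum tacrolimus value > 15 in 7 days, present or absent major" bleeding. It gives no time window for bleeding and no start point for the antibiotic period. It does not describe any of the comparisons as descriptive or non-randomised.

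Two of these variables also appear as outcomes. The Secondary objective includes "liver graft dysfunction (initial poor" function subtype, and primary nonfunction. Under Other outcomes (safety): "The safety outcomes to be assessed are the incidence of major postoperative" bleeding at 7 days.

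**The concern.** A subgroup comparison keeps the protection of randomisation only if membership is settled before allocation, or cannot be altered by it. The protocol lists graft dysfunction and postoperative bleeding as outcomes, so it accepts that the pressure target might change them. Using the same variables to divide patients conditions on a possible effect of treatment. Patients who bleed under the higher target may then differ in underlying risk from those who bleed under the lower one, and a difference in renal dysfunction between arms within that stratum can be pure selection.

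At stake is the reading of the subgroup tables. A benefit or harm reported for patients with graft dysfunction or bleeding could be taken as guidance on who should receive the higher target, and such a group cannot be identified when the target has to be chosen.

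**Working it through.** **Step 1: date each subgroup variable against randomisation (within 2 hours of ICU admission, after surgery).**

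- Previous renal dysfunction: baseline.
- Home or hospitalised: baseline. Data collection records "origin before transplantation (ICU, ward or home").
- Liver graft dysfunction: after randomisation. Appendix 1 uses, for example, "bilirubin > 10mg/dL on the seventh day after" transplantation, and events up to day 10 for primary nonfunction. It is a secondary outcome.
- Tacrolimus above 15 in 7 days: after randomisation, by its own wording.
- Major bleeding: the only definition in the article (Appendix 1) is postoperative, and it is a safety outcome. However, Statistical analysis names intraoperative major bleeding as an adjustment variable, and the subgroup text sets no window. Plain reading: after randomisation, but not fixed.
- Antibiotics for more than 48 hours: a duration, normally complete only after randomisation. The start point is not stated, and General management says prophylaxis is decided before randomisation. Plain reading: after randomisation, but not fixed.

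Count: two certain (one a trial outcome), up to four (two of them trial outcomes).

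Graft dysfunction also overlaps with the primary outcome. Death within 7 days counts as a primary event, and death from a nonfunctioning graft is part of the nonfunction definition. One such death therefore both assigns the subgroup and sets the outcome.

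**Step 2: the plan's own sample size, for scale.** Inputs from Sample size calculation: 73.7% v 53.7%, power 80%, alpha 5% (taken as two-sided). With unpooled variance, n per arm = (1.960 + 0.842)² × (0.737×0.263 + 0.537×0.463) / 0.20² = 7.849 × 0.4425 / 0.04 = 86.8, so 87 per arm and 174 in total. The stated figure is reproduced.

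**Step 3: size of the false effect, illustration A.** All inputs are assumed except the 73.7% mean. Half the patients are low risk (57.4% renal dysfunction) and half high risk (90%). Treatment has no effect on renal dysfunction. In controls the subgroup event occurs in 10% of low-risk and 50% of high-risk patients. The intervention raises it in low-risk patients only.

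Risk among those with the event = (s_L×0.574 + s_H×0.90)/(s_L + s_H), where s_L and s_H are the event rates in low- and high-risk patients. For those without it, use 1 − s_L and 1 − s_H.

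- Control: with event (0.0574 + 0.45)/0.60 = 84.6%; without (0.5166 + 0.45)/1.40 = 69.0%.
- Event +10 points: with event (0.1148 + 0.45)/0.70 = 80.7%, false difference −3.9; without (0.4592 + 0.45)/1.30 = 69.9%, false difference +0.9.
- Event +20 points: with event (0.1722 + 0.45)/0.80 = 77.8%, false difference −6.8; without (0.4018 + 0.45)/1.20 = 71.0%, false difference +1.9.
- Event unchanged: both differences are exactly 0.

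**Step 4: illustration B, a smooth model.** Logit of bleeding = −1.5 + gU + b×arm; logit of renal dysfunction = 1.15 + gU, with no arm term; U standard normal; g = 1.0 to 1.5; b = 0.5 to 0.8. By numerical integration, renal dysfunction is 69–72% in both arms, and bleeding rises from 22–25% to 30–38%. The false differences are −1.0 to −2.4 points in bleeders and −1.1 to −3.2 in non-bleeders. The gap between strata is only 0.1 to 0.8 points.

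**Step 5: set against sampling error at 87 per arm.**

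- Illustration A, event +10: 26.1 v 30.45 patients with the event; SE = √(0.846×0.154/26.1 + 0.807×0.193/30.45) = 10.1 points; bias/SE = 3.9/10.1 = 0.39.
- Illustration A, event +20: 26.1 v 34.8 patients; SE = √(0.846×0.154/26.1 + 0.778×0.222/34.8) = 10.0 points; bias/SE = 6.8/10.0 = 0.68.
- Illustration B: SE 9.6–11.4 points in bleeders and 8.2–8.9 in non-bleeders; bias is at most 3.2/8.9 = 0.36 of an SE.

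**The case against.** The strongest reply has four parts.

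1. **The count.** A reader might infer that exactly four of six subgroups are post-randomisation. The text does not settle that. Bleeding could mean the intraoperative variable named under Statistical analysis, and the antibiotic grouping could follow the regimen chosen before randomisation. This stands, so the firm count is two. Graft dysfunction and tacrolimus remain whichever way the other two are read.

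2. **The size.** A reader might infer that the plan will produce a misleading subgroup claim. The illustrations do not show that. Every behavioural input is assumed. Bias is zero if the target does not move the subgroup variable, and nothing in the article bears on whether it moves antibiotic duration or tacrolimus level. In illustration B the two strata shift almost equally, so no subgroup difference would stand out. At this sample size noise exceeds bias in every case shown. This stands as a limit on magnitude. It does not restore the protection of randomisation.

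3. **Exploratory status.** Statistical analysis calls the secondary outcomes exploratory. That wording does not extend to the subgroups, and labelling an analysis exploratory deals with multiplicity, not with selection.

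4. **A condensed article.** The full document may say more. The point, however, is not an omission: the article itself fixes these variables as planned subgroups and says they were sent to the ethics committee.

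**Conclusion.** The point holds in a limited form. Two planned subgroups, liver graft dysfunction and tacrolimus above 15 in 7 days, are certainly formed after randomisation, and one of them is a secondary outcome. On the plain reading major bleeding and antibiotics beyond 48 hours join them, making up to four. Treatment comparisons within these groups can be biased if the pressure target alters membership. Such an effect is plausible for bleeding and graft function and less clear for antibiotics and tacrolimus.

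Under the assumed inputs the larger false difference in each scenario is about 1 to 7 points, and its sign and size depend on assumptions that the article does not supply. Relative to sampling error this is at most about 0.7 of a standard error.

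A reader might also infer that the trial's main conclusion is at risk. It is not: the primary intention-to-treat comparison does not use these groupings, and the article's stated conclusions rest on the overall result. Severity is moderate.

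**What to change.** - Limit treatment-effect subgroup analyses to variables known before randomisation: previous renal dysfunction, and home or hospitalised. Test each by a treatment-by-subgroup interaction.
- Define the bleeding subgroup as intraoperative bleeding, for example from the intraoperative blood-product data already listed under Data collection, or drop it. That list has no variable called intraoperative major bleeding, so the rule for deriving it must be written down.
- Define the antibiotic subgroup by the regimen set before randomisation, or drop it.
- Report graft dysfunction, postoperative bleeding, antibiotic duration and tacrolimus level by arm as outcomes or process measures. Label any grouping of patients by them descriptive and non-randomised.
- Do not substitute MELD score or donor risk index as if they were equivalents. They are baseline variables, but they would be new subgroups.

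The cost is a change of wording and a notice to the ethics committee. Up to four planned subgroup tables are lost or relabelled. Recruitment stood at 67.8% on February 28, 2023, so the change should be dated and made before outcomes are examined by arm.
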